#### Strategies to improve adherence to interventions {11c}

This is a pragmatic trial. While site coordinators will facilitate the initial steps for receipt of care for ICAU and the digital CBTI hub, no study-specific standardized strategies or procedures will be used to ensure participant attendance or compliance with treatment sessions or CBTI techniques. ICAU clinicians will continue any existing strategies typically used at their site and that they have found helpful to support adherence to treatment. Digital CBTI hub clinicians will use the just-in-time monitoring capabilities embedded in the COAST platform and prompt participants when they have missed logging their sleep on the COAST patient app. The COAST patient app includes reminders to complete the sleep diary to facilitate data collection.

#### Relevant concomitant care permitted or prohibited during the trial {11d}

Participants may receive care for comorbid psychiatric and medical conditions to the extent that eligibility criteria for the trial continue to be met. Specific details are provided above in the “Eligibility criteria {10}” section.

#### Provisions for post-trial care {30}

The anticipated risks for participants are believed to be minimal. Throughout this study, all procedures and techniques involve no more than minimal risk and are the same as would be expected from the traditional in-person sleep intervention. The participant’s sleep provider will make determinations about any further care required for the participant following a course of CBTI or if it is deemed participation in CBTI should be terminated.

### Outcomes {12}

The primary outcome measure is the Insomnia Severity Index (ISI) [46, 47]. The ISI is a 7-item self-report questionnaire that assesses the subjective severity of insomnia symptoms, degree of satisfaction with sleep, and nature and noticeability of daytime impairments. Each item is rated on a 0 to 4-point scale. A score of 15 or greater reflects clinically significant insomnia. All participants will be administered the ISI at baseline, 6–8 weeks later, and then again at 3-month follow-up.

To assess the changes in depression and anxiety symptom severity, the Patient Health Questionnaire-2 items (PHQ-2) [48, 49] and the Generalized Anxiety Disorder-2 items Scale (GAD-2) [50] will be used. The PHQ-2 assesses depressed mood and anhedonia, which are the first two items of the 9-item version of the Patient Health Questionnaire. The score ranges from 0 to 6, and a total score of greater than 3 indicates likely major depressive disorder. The GAD-2 assesses the severity of feelings of nervousness and worry on a score of 0 to 3 for each of the 2 items. A total score of greater than 3 has been shown to have good sensitivity and specificity for anxiety disorders. All participants will be administered the PHQ-2 and the GAD-2 at baseline, 6–8 weeks later, and at 3-month follow-up.

Satisfaction with insomnia treatment will be assessed using two measures including an adapted version of the Insomnia Treatment Acceptability Scale (ITAS) [51] and the Client Satisfaction Questionnaire [52]. An adapted version of the ITAS will be used to assess overall perceived acceptability and treatment preferences for either of the two CBTI modalities. On the ITAS, both treatment options will be described, and participants will be asked to rate identically worded questions about the acceptability of the treatment for oneself and others, likelihood of adhering to treatment recommendations, and expectations of short- and long-term treatment effectiveness for specific insomnia symptoms (e.g., difficulty falling or staying asleep), expected impact of insomnia treatment on daytime symptoms of insomnia, and severity of expected side effects. These items are rated for both treatments, both of which are scored on a 10-point scale. The total score for each subscale is the average of the 8 items, with higher scores indicating greater willingness to utilize the treatment. Reported Cronbach’s values for the scales are greater than 0.80. For this trial, we will contrast responses to ICAU and digital CBTI hubs. The Client Satisfaction Questionnaire is an 8-item survey that assesses the perceived quality of care, services, and clinicians encountered during treatment. Higher scores indicate greater satisfaction. Both satisfaction surveys will be administered at 6–8 weeks only.

#### Participant timeline {13}

The total duration of participation is up to 5 months. Figure 1 displays the schedule of enrollment, interventions, and assessments for the primary outcomes of interest.

**Fig. 1 Fig1:**
[figure not shown]
Schedule of enrollment, interventions, and assessments for study participants

#### Sample size {14}

Power calculations and sample size were based on a conservative estimate of the non-inferiority margin (NIM) based on our preliminary data and prior studies [53–55] and effect sizes reported in the literature on the effects of CBTI on insomnia severity [56–60], as well as estimates of recruitment feasibility based on patient volume at the participating sites. Specifically, effect sizes in the moderate to very large range (0.50 to 2.15) have been reported for insomnia, depression, and anxiety in military and civilian samples. Thus, we conservatively estimated a NIM of *d* = 0.5 for each outcome of interest for this trial. The NIM of |*d*|= 0.5 set to determine non-inferiority is stringent as it represents 50% of the effect size reported in recent meta-analyses [61–63]. For non-inferiority tests, we set an allowable one-sided type I error rate of *α* = 0.025. Conservatively adjusting for our two a priori *t*-tests (post-treatment and a 3-month follow-up), we use *α** = 0.0125 to determine power. Based on the current patient volume and clinical workflows at the three participating sites, we estimated that a total of 188 patients could be enrolled in this clinical trial over the period of performance. Power calculations using PASS version 23.0.2. [64] yielded 88% power with a full sample of 94 participants per group (our primary strategy and 80% power with a final sample of 140 completers assuming an attrition rate of 25% (*N* = 70 completers per group).

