## Statistical methods

### Statistical methods for primary and secondary outcomes {20a}

Preliminary data analyses will be performed prior to testing the aims to check for collinearity of covariate and outcome measures, to ensure completeness and accuracy of data, and to evaluate distributions. The primary and secondary aims will be tested with non-inferiority hypotheses of the general form: H0: digital CBTI hubs are inferior to ICAU versus H1: digital CBTI hubs are non-inferior ICAU. For each outcome, we will calculate the standardized differences (Cohen’s *d*) as digital CBTI hubs—ICAU, such that a positive difference is in favor of ICAU if higher values are worse, and a negative difference is in favor of ICAU if higher values are better. Since higher values indicate worse outcomes for our measures of interest (e.g., ISI, depression, anxiety), we will use a non-inferiority margin (NIM) of 0.50 and declare digital CBTI hubs to be non-inferior to ICAU if the upper bound of the 95% confidence interval (CI) for *d* is ≥ 0.50. We will declare digital CBTI hubs to be inferior to ICAU if the upper bound of the 95% CI for *d* is ≤  − 0.50. For example, if *d* (95% CI) = 0.10 (− 0.20, 0.40), we would declare digital CBTI hubs as non-inferior to ICAU because 0.40 < 0.50. But if *d* (95% CI) = 0.40 (0.10, 0.70), we would declare digital CBTI hubs to be inferior because − 0.70 ≥ 0.50. These one-sided decision rules equate to requiring the effect size comparing digital CBTI hubs to ICAU to have no more than moderate strength (|*d*|= 0. 5) in favor of ICAU.

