Our primary strategy will compare digital CBTI hubs and ICAU using analyses that are straightforward and highly interpretable while still accounting for other important covariates. We will use analysis of covariance (ANCOVA) to determine whether ISI at 6–8 weeks and at 3-month follow-up differs between digital CBTI hubs and ICAU after controlling for baseline ISI and other relevant covariates. Cohen’s *d* effect sizes (*d* ESs) with 95% CIs estimated from the ANCOVA model will be calculated and compared to the NIM as outlined above. To examine more nuanced effects across time, we will calculate the rate of change in ISI symptoms (ΔISI) across baseline, 6–8 weeks, and 3-month follow-up for each individual and then use linear regression to compare ΔISI between digital CBTI hubs and ICAU after controlling for relevant covariates. We will also model the repeatedly measured outcome using mixed effects models with a random intercept and slope. Cohen’s *d* ESs and 95% CIs estimated from these models will be calculated and compared to the NIM as outlined above.

For non-inferiority tests, we set an allowable one-sided type I error rate of *α* = 0.025. Conservatively adjusting for our two a priori *t*-tests (6–8 weeks and 3-month follow-up), we use *α** = 0.0125 to determine power. Our full sample size of 94 per group will provide 0.88 power. However, even with attrition of 25% (*N* = 70 completers per group), we expect to have 0.80 power. We will use the same statistical approach to assess and compare changes in depression and anxiety symptom severity at 6–8 weeks and at 3-month follow-up.

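### The rate-of-change analysis should not be judged against the 0.5 margin, since it gives the 6–8 week score almost no weight, and the margin's 50% defence holds only for an effect of 1.0

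*Protocol article*

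**What the plan says.** Sample size {14} gives one range for three outcomes together: "effect sizes in the moderate to very large range (0.50 to 2.15) have been reported for insomnia, depression, and anxiety in military and civilian samples". From that range it concludes: "Thus, we conservatively estimated a NIM of *d* = 0.5 for each outcome of interest for this trial". It adds that the margin "is stringent as it represents 50% of the effect size reported in recent meta-analyses", without naming the outcome that those meta-analyses measured.

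Statistical methods for primary and secondary outcomes {20a} repeats the figure for ISI, depression and anxiety: "we will use a non-inferiority margin (NIM) of 0.50". The primary strategy is an ANCOVA of ISI at 6–8 weeks and at 3-month follow-up. To look at change over time, the plan will also "calculate the rate of change in ISI symptoms (ΔISI) across baseline, 6–8 weeks, and 3-month follow-up for each individual" and use "linear regression to compare ΔISI between digital CBTI hubs and ICAU after controlling for relevant covariates". Mixed models with a random intercept and slope follow. The effect sizes "estimated from these models will be calculated and compared to the NIM as outlined above". Depression and anxiety are to be handled in the same way.

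Trial design {8} places the first follow-up 6–8 weeks after baseline and the second 3 months after that. This agrees with the participation of up to 5 months given under Participant timeline {13}.

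**The concern.** Two things are fixed badly.

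(a) A margin has meaning only on the scale for which it was justified. This one is justified, if at all, for a difference in symptom level. A per-person slope over three unevenly spaced visits is a different quantity: it is almost the last score minus the first. Comparing its d with 0.5 gives a second non-inferiority verdict that barely uses the 6–8 week visit, one of the two time points of the first hypothesis. That d is also divided by the SD of slopes, and the protocol offers no effect size on that scale.

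(b) The words conservative and stringent rest on the margin being half of an effect, but they are applied to every outcome. The same paragraph reports effects as low as the margin itself. A reader of a non-inferior result for PHQ-2 or GAD-2 could believe that half of the benefit is assured when the document does not show this.

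**Working it through.** **Inputs from the protocol.** Margin 0.5; effect range 0.50 to 2.15; 94 per group; one-sided alpha 0.0125 for power; visits at baseline, 6–8 weeks and 3 months later, taken as weeks 0, 7 and 20 (7 + 13).

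**Assumptions, not in the protocol.** ISI SD of 6 at each visit; the same correlation r between any two visits, with r = 0.3, 0.5 or 0.7. For power: SD 1 and a true difference of 0.

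**The plan's own figure.** Normal-approximation power is Φ(0.5/√(2/94) − 2.241) = Φ(1.187) = 88.2%; the noncentral t gives 87.8%. The stated 88% is reproduced, so the margin is read on the intended scale.

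**Slope weights.** The weight of each score is (t − mean t)/Σ(t − mean t)².

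| Visits (weeks) | Baseline | 6–8 weeks | 3-month follow-up | Divisor |
|---|---|---|---|---|
| 0, 6, 19 | −8.3 | −2.3 | 10.7 | 188.7 |
| 0, 7, 20 | −9 | −2 | 11 | 206 |
| 0, 8, 21 | −9.7 | −1.7 | 11.3 | 224.7 |
| coded 0, 1, 2 | −1 | 0 | 1 | 2 |

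A higher (worse) 6–8 week score leaves the slope unchanged or makes it look slightly better. Adjusting for baseline ISI does not alter the sign of the middle weight.

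**Scenario.** The hub is worse by 3.6 ISI points (0.6 × 6) at 6–8 weeks and equal at the other two visits.
- Slope difference = −2 × 3.6/206 = −0.035 points per week.
- Slope SD = 6 × √((1 − r)/206) = 0.35, 0.30, 0.23 for r = 0.3, 0.5, 0.7.
- Slope d = −0.10, −0.12, −0.15, all in the hub's favour. The assumed SD of 6 cancels, so only the 0.6 SD and r matter.
- Over weeks 0/6/19 to 0/8/21, d = −(middle weight × 0.6)/√((1 − r) × divisor). This runs from −(1.67 × 0.6)/√(0.7 × 224.7) = −0.08 to −(2.33 × 0.6)/√(0.3 × 188.7) = −0.19.

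**Scale of the margin.** For a difference at 3-month follow-up only, a slope d of 0.5 corresponds to 0.5 × slope SD × 206/11 = 3.3, 2.8 and 2.1 ISI points for r = 0.3, 0.5 and 0.7. The same 0.5 on the score scale is 0.5 × 6 = 3.0 points. The shift is modest, but its size depends on a correlation that the plan does not state.

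**Share of the effect protected.** If non-inferiority is shown, the share kept exceeds 1 − 0.5/effect.

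| Effect | Margin as share of effect | Share kept exceeds |
|---|---|---|
| 0.50 | 100% | 0% |
| 0.80 | 62.5% | 37.5% |
| 1.00 | 50% | 50% |
| 2.15 | 23% | 77% |

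The 50% statement is true in one row only.

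**The case against.** The strongest reply to (a) is that the slope is a supporting analysis. The ANCOVA at each visit is primary, and in the scenario above the true 6–8 week difference exceeds the margin, so that ANCOVA would very rarely declare non-inferiority. This stands: a reader might infer that the slope analysis could carry an inferior hub through the trial, and the protocol does not support that. It is also fair that the protocol does not fix the time coding and does not say that time is linear in the mixed model. That helps little. Coding visits 0, 1, 2 brings the middle weight only to zero, and a per-person rate of change over three visits is a slope whatever the software.

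The strongest reply to (b) concerns what a margin equal to the effect implies. A reader might infer that a non-inferior result for depression or anxiety could stand although the hub has no benefit at all. That does not follow at an effect of 0.50. Taking the decision rule as the section's first worked example applies it (upper limit below 0.50), total loss is excluded. A hub with no benefit would sit on the null boundary and pass at most 2.5% of the time, and with 94 per group the observed d must be about 0.21 or less. Nor can a reader assign 0.50 to depression or anxiety: the range pools outcomes and populations, and the 50% is tied to meta-analyses that are not reproduced in the document. The suggestion that treated participants have little mood change left to preserve is likewise conjecture.

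**Conclusion.** The point holds in a limited form, and the change is worth making.

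(a) A slope-based d should not be compared with the 0.5 margin. It ignores or slightly reverses a 6–8 week deficit (about −0.10 to −0.15 for a true loss of 0.6 SD), and the plan supports no margin on the slope scale. This rests on least-squares slopes over calendar time, the assumed equal correlations and, for the mixed model, a linear time effect. The primary ANCOVA is unaffected.

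(b) The description of 0.5 as conservative, and as stringent at 50% of the effect, holds only for an effect of 1.0. At the bottom of the plan's own range the guarantee falls to more than 0%. The protocol neither places depression or anxiety there nor says whether the reported effects are against a control or pre-post, and a preserved share needs the former. Preservation of half of the effect is therefore unsupported for the secondary outcomes rather than shown to fail. The ISI margin at a single visit may well be adequate and is not disputed here.

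**What to change.** **Statistical methods {20a}.** Remove the comparison with the margin for the per-person rate of change and the random-slope models. Instead, fit a mixed model with visit as a category, report the arm contrasts at 6–8 weeks and at 3-month follow-up, standardise them by the SD used for the primary ANCOVA, and compare those with 0.5. Do the same for PHQ-2 and GAD-2. The cost is slight recoding and the loss of a single slope summary.

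**Sample size {14}.** Restrict the 50% and stringent wording to the outcome whose cited effect is about 1.0. For PHQ-2 and GAD-2, state what share of the effect 0.5 preserves according to the cited sources, report the adjusted difference with its confidence interval, and word any non-inferiority conclusion to match. Hypothesis 2 need not be deleted.

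Tightening the margin instead would not be free. If a secondary effect really were 0.50, half of it is 0.25, and power with 94 per group would be about 30% at one-sided alpha 0.0125, or 40% at 0.025. Stating the preserved share openly costs only wording.

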### Methods for additional analyses (e.g., subgroup analyses) {20b}

If non-inferiority is established, we will conduct secondary tests to determine whether digital CBTI hubs may also be superior to ICAU.

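### One-sided 0.025 is halved for two visits, yet non-inferiority is declared outcome by outcome on a 95% interval, with no order or gate across outcomes

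*Protocol article*

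**What the plan says.** Sample size {14} sets the level: "For non-inferiority tests, we set an allowable one-sided type I error rate of" 0.025. It continues "Conservatively adjusting for our two a priori" t-tests, meaning post-treatment and 3-month follow-up, and arrives at "0.0125 to determine power". The two tests are identified by visit. The sentence does not name the ISI, and the margin of d = 0.5 is set for every outcome. Statistical methods {20a} repeats the split.

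Statistical methods {20a} also fixes how a claim is made: "The primary and secondary aims will be tested with non-inferiority hypotheses of the general form", with the 95% interval for d compared with 0.50. The printed inequality is garbled, but the worked example shows the intent: "we would declare digital CBTI hubs as non-inferior to ICAU because 0.40 < 0.50". The ISI plan is then extended: "We will use the same statistical approach to assess and compare changes in depression and anxiety symptom severity" at both visits.

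Objectives {7} states three non-inferiority hypotheses, on insomnia, on depression and anxiety, and on satisfaction. For the third, Outcomes {12} says "Satisfaction with insomnia treatment will be assessed using two measures", given at 6–8 weeks only. The same section names the ISI as the primary outcome. Additional analyses {20b} adds "If non-inferiority is established, we will conduct secondary tests to determine whether digital CBTI hubs may also be superior to ICAU".

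**The concern.** Two things do not fit together. First, the alpha split counts two tests, while the same declaration rule serves about eight: ISI at two visits, PHQ-2 at two, GAD-2 at two, and two satisfaction instruments. Nothing makes a depression, anxiety or satisfaction claim depend on the ISI. Second, 0.0125 is used for power, but decisions rest on a 95% interval, so the split never reaches the decision rule.

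At stake is what may be claimed. A hub that fails on insomnia, the condition being treated, could still be reported as non-inferior on one short mood scale at one visit, at an error rate the article does not state.

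**Working it through.** **Inputs from the article.** One-sided 0.025; split over two visits; margin d = 0.5 for each outcome; 95% interval as decision rule; 94 per group, or 70 completers per group.

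**Inputs assumed.** True differences at the margin for error rates, and zero for power. The article gives no correlations between test statistics, so a range is used. The high case has 0.8 between visits of a scale, 0.7 between scales at the same visit (0.8 × 0.7 = 0.56 across both) and 0.5 for satisfaction. The low case is independence.

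**The plan's own figures.** 0.025 / 2 = 0.0125, as stated. Power is Φ(0.5/√(2/n) − z), with z = 2.241 at one-sided 0.0125. For n = 94: Φ(3.428 − 2.241) = Φ(1.187) = 88%, as stated. So 0.0125 is the level behind the headline power. (For n = 70 the same formula gives Φ(2.958 − 2.241) = 76%, not the stated 80%; that is a separate matter.)

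**Level of the decision rule.** The upper bound of a two-sided 95% interval is a one-sided test at 0.025. One-sided 0.0125 needs a two-sided 97.5% interval.

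**Chance of at least one false claim among k tests.** With independent tests this is 1 − (1 − a)^k. For hypothesis 2 (k = 4), 1 − 0.9875⁴ = 4.9% and 1 − 0.975⁴ = 9.6%; the Bonferroni ceilings are 4 × 0.0125 = 5.0% and 4 × 0.025 = 10.0%. For k = 2, 1 − 0.9875² = 2.5% and 1 − 0.975² = 4.9%. The high-correlation values come from simulating correlated normal test statistics.

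| Any single success counts | 0.0125 per test | 95% interval (0.025 per test) |
|---|---|---|
| Hypothesis 1: ISI, 2 tests | 2.0–2.5% | 3.9–4.9% |
| Hypothesis 2: PHQ-2 and GAD-2, 4 tests | 3.4–4.9% | 6.4–9.6% |
| Hypothesis 3: satisfaction, 2 tests | 2.3–2.5% | 4.5–4.9% |

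The lower end of each range is the high-correlation case and the upper end is independence. The hypothesis 3 row assumes that the ITAS is compared between arms.

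**If all components must succeed.** The chance that every test falsely passes cannot exceed the per-test level, so it is at most 2.5% under the 95% interval, whatever the correlation.

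**The case against.** The strongest reply is that the article means 0.025 per outcome, shared between two visits. The split is defined by visit, the margin is set for each outcome, and the mood scales follow the same approach. On that reading, with 0.0125 applied at each visit, ISI, PHQ-2 and GAD-2 each keep 2.5%. This stands as a possible reading. It also means that the split should not be described as confined to the ISI, because the text does not say so.

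Second, the ISI is the single primary outcome. Leaving secondary outcomes unadjusted is common, and so is placing their hierarchy in an analysis plan, which is not shown here. A missing hierarchy alone would therefore be no finding. What remains is what the article does state: formal declarations on secondary aims by the primary rule, and an interval that does not carry the stated split, for the ISI or any other outcome.

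Third, the inflation needs any single success to count. Objectives {7} joins the visits, and depression with anxiety, by a plain conjunction. If all must succeed, nothing inflates. The article does not settle this.

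Fourth, the count of eight is inferred. On the ITAS each participant rates both treatments, so that contrast may be within person. Superiority tests add no burden either: on an outcome that has already passed non-inferiority they need no extra alpha.

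**Conclusion.** The concern holds in a limited form. The stated split (0.0125) and the stated decision rule (95% interval) disagree, and no order or gate links the outcomes on which non-inferiority is declared. If any single result supports a claim, hypothesis 2 exceeds 2.5% under either per-test level: about 3.4 to 4.9% at 0.0125 and 6.4 to 9.6% under the 95% interval. Hypotheses 1 and 3 exceed it only under the 95% interval, at 3.9 to 4.9% and 4.5 to 4.9%. These ranges rest on differences at the margin and on assumed correlations.

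A reader might go further and say that the trial breaches a promised overall 0.025, citing the chance of any false claim over all eight tests (6.0 to 9.6% at 0.0125; about 10.8 to 18.3% under the 95% interval). The article does not support that: it never sets 0.025 as a level across hypotheses, and the eighth test may not be a between-arm comparison. Nor does it support saying that satisfaction exceeds the level at 0.0125 per test.

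**What to change.** State one scheme and make the intervals follow it.

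1. Make the ISI the gatekeeper at one-sided 0.025, and say whether its two visits are separate claims. If they are, use Holm: compare the visit with the stronger result using a 97.5% interval and, if it passes, the other using a 95% interval. If both visits must succeed for a single claim, 95% intervals at both already keep 2.5%.
2. Declare non-inferiority on PHQ-2, GAD-2 and satisfaction only after the ISI has succeeded at both visits, so that the full 0.025 passes on. Test them in an order the sponsor fixes in advance, with Holm over the visits of a scale, and stop at the first failure. Say which satisfaction measure carries the claim and whether the ITAS contrast is between arms.
3. After a failure, report the remaining outcomes as estimates with intervals, without a declaration.
4. Superiority on an outcome that has passed non-inferiority can stay as planned, without extra alpha.

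The ISI loses none of its planned power. With equal arms and an assumed correlation of 0.6 between visits, replacing Bonferroni by Holm raises the chance that both ISI visits pass from 0.81 to 0.88 at 94 per group, and from 0.65 to roughly 0.75 at 70. By contrast, Bonferroni over eight tests (0.025 / 8 = 0.003125 each) would leave about 75% power per test at 94 per group.

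The cost is a paragraph in the protocol or analysis plan. The downsides are that no formal secondary claim is possible if the ISI or an earlier step fails, and that Holm has no simple simultaneous confidence intervals, which matters in a plan that decides by intervals.

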#### Plans to promote participant retention and complete follow-up {18b}

The retention of participants for the follow-up period can be challenging. We will employ strategies that allowed us to complete post-intervention procedures and achieve high levels of adherence (> 80%) in previous studies, including, for example, participation gratitude letters [53–55].

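### The stated 80% power with 70 completers per group does not follow from the plan's own inputs, which give about 75–76%

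*Protocol article*

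**What the plan says.** In the protocol article, *Sample size {14}* sets out the basis for power. The margin is d = "0.5 for each outcome of interest for this trial". On error rates the section says "we set an allowable one-sided type I error rate of" 0.025. It then halves this for two time points ("Conservatively adjusting for our two a priori" t-tests, post-treatment and 3-month follow-up) and uses "0.0125 to determine power". The calculation "yielded 88% power with a full sample of 94 participants per group", and also "80% power with a final sample of 140 completers assuming an attrition rate of 25" percent, which the section gives as 70 per group.

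*Statistical methods for primary and secondary outcomes {20a}* repeats the same alpha and both sample sizes. Of the 70-per-group case it says "we expect to have 0.80 power".

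Neither section states a true difference between arms, a covariate correlation, or a second alpha for the completer figure.

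**The concern.** The two powers are presented as one calculation at two sample sizes, with the same alpha, margin and test. Losing a quarter of the sample should cost more than the eight points the article shows. If the first figure is right on the stated inputs, the second looks too high.

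The completer figure is the article's only assurance that 188 enrolled participants still give the conventional 80% after dropout. A reader judging how much attrition the design can bear would rely on it, and would believe that 25% is tolerable when, at the alpha chosen for power, it is not.

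**Working it through.** **Inputs.** Margin d = 0.5 on a standardized scale (SD = 1), one-sided alpha 0.0125, a two-sample t-test, and 94 or 70 per group, all from *Sample size {14}*. Allocation is 1:1, from *Sequence generation {16a}*. The true difference is assumed to be 0; the article does not give it.

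**Formulas.** Normal approximation: power = Φ(0.5·√(n/2) − z), with z = 2.241 for one-sided 0.0125. The t version uses a noncentral t with 2n − 2 degrees of freedom and noncentrality 0.5·√(n/2).

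**Step 1: reproduce the 88%.** For n = 94, 0.5·√47 = 3.428.
- Normal: Φ(3.428 − 2.241) = Φ(1.186) = 0.882.
- Noncentral t: 0.878.

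Both round to the stated 88%, which supports the zero true difference.

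**Step 2: the same inputs at 70 per group.** 0.5·√35 = 2.958.
- Normal: Φ(2.958 − 2.241) = Φ(0.717) = 0.763.
- Noncentral t: 0.755.

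The stated 80% does not reproduce.

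**Step 3: look for inputs that give both figures** (noncentral t).

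| Inputs | 94 per group | 70 per group |
|---|---|---|
| Stated in the article | 88% | 80% |
| Alpha 0.0125, true difference 0 | 87.8% | 75.5% |
| Alpha 0.025, true difference 0 | 92.6% | 83.6% |
| Alpha about 0.018, true difference 0 | 90.6% | 80.0% |
| Alpha 0.0125, covariates explaining 10% of variance | 91.1% | 80.2% |
| Alpha 0.025, true difference 0.02 against the hub | 90.6% | 80.5% |
| Alpha 0.025, Wilcoxon (relative efficiency 0.955) | 91.5% | 81.9% |

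Every variant that reaches about 80% at 70 per group gives about 91% at 94. In the other direction, tuning alpha or the standardized distance so that 94 per group gives 88% leaves 76–77% at 70. Rounding does not close the gap: 88.5% at 94 corresponds to at most 78% at 70.

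**Step 4: what 80% needs at alpha 0.0125.** Normal: n = 2·((2.241 + 0.842)/0.5)² ≈ 76.04, so 77 per group. By noncentral t, 77 gives 79.8% and 78 gives 80.4%, so 78 per group. From 94 randomized per arm, that allows attrition of (94 − 78)/94 = 17%.

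**Step 5: the attrition arithmetic.** 188 × 0.75 = 141, and 70/0.75 = 93.3, which rounds up to 94. This part is right; only the power attached to 70 is wrong.

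**The case against.** **The trial will not be tested at 0.0125.** The article uses that alpha only to determine power. Its decision rule in *Statistical methods {20a}* compares a 95% confidence bound with the margin. (One inequality sign there is reversed, but the first worked example shows the intent.) That is a one-sided test at 0.025, with power of 83.6% (t) or 84.1% (normal) at 70 per group. This stands, and it limits the consequence. A reader might infer that, with 70 completers and equal arms, the trial misses non-inferiority about 1 time in 4. That holds only if the test is run at 0.0125. Under the 95% interval as written, the chance at one time point is about 1 in 6.

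**The primary analysis is ANCOVA, not a t-test.** If covariates explained 10% of outcome variance (an assumption; the article gives no figure), power at 70 per group and 0.0125 would be 80.2%, and at 20% it would be 85.0%. This stands as a reason to expect a modest practical effect. It does not rescue the stated figure, because the article bases power on t-tests and claims no such gain, and the same gain would lift the 94-per-group figure to 91%.

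**Attrition of 25% is a contingency.** A reader might infer that the plan itself does not expect the 88% to apply. The article calls the full sample its primary strategy and plans an intent-to-treat analysis, so that reading goes too far.

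**Past retention.** *Plans to promote participant retention {18b}* mentions strategies that helped "achieve high levels of adherence (> 80%) in previous studies". A reader might take this as an 80% retention target. It concerns earlier studies and sets no target for this trial. For scale only, 75 per group would give 78.7% at 0.0125.

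**Conclusion.** The completer power is wrong as written, in both places where it appears. On the article's own alpha, margin and test, 70 per group gives about 75–76% rather than 80%, a shortfall of 4–5 points. The result assumes a true difference of zero, which the article does not state but which reproduces its 88%. A true difference against the digital hub would lower the power further. The incompatibility of the two figures does not hang on that assumption, since no set of inputs tried yields both.

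This is an error in a reported figure. It does not establish that the trial is underpowered as it will be analysed, and it does not call for more participants: the article presents 188 as what the sites could enrol, not as the solution for 80% power.

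**What to change.** In *Sample size {14}* and *Statistical methods {20a}*, replace the completer statement with: 88% power if all 188 participants provide the outcome; about 75% with 70 completers per group; 80% requires 78 completers per group, that is, attrition of at most about 17%. State the assumed true difference (zero, if that was used).

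Two alternatives need their own wording:
- If the authors rely on a gain from ANCOVA, give the assumed R-squared and apply it to both sample sizes.
- If the 95% interval rule (one-sided 0.025) is the intended test, restate power as about 93% with 94 per group and 84% with 70 per group, for each time point.

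The cost is two reworded sentences and, if power stays at alpha 0.0125 without a covariate gain, a slightly less favourable figure. Sample size, margin and analysis stay as they are.
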